### Quality control

Before the trial, all staff members are required to attend a series of training sessions. These sessions will ensure that the personnel involved fully understand the research protocol and standard operating procedures for the study. To maintain the clinical trial at a consistently high quality, the clinical research center of Longhua Hospital will monitor the study file, informed consent forms, case report forms (CRFs), serious AEs, and data records regularly.

### Data collection, management, and monitoring

The CRF, Treatment Form, and Adverse Events Form will be first completed and then double-entered into the electronic data capture (EDC) system electronically by two independent investigators to act as the first level of control to ensure the accuracy of the data. The second level of data integrity will include data monitoring and validation, which will be conducted on a regular basis throughout the study. The original CRFs and all other forms (including the consent forms) will be archived securely in the clinical research center of Longhua Hospital, affiliated with the Shanghai University of TCM for 5 years following publication of the last paper or report from the study.

The safety of the study will be monitored by a Data and Safety Monitoring Board (DSMB) of the clinical evaluation center of Longhua Hospital, affiliated with Shanghai University of TCM, which consists of independent clinical experts and statisticians with access to unblinded data. The DSMB is independent from the sponsor, the competing interests, and the investigational site and will review the performance and safety of the trial monthly.

The criteria for unblinding and discontinuing allocated interventions for a given trial participant include having a recurrent stroke, having serious complications of stroke or experiencing serious acupuncture-related AEs (if any), which have been described previously. The DSMB will reveal a participant’s allocated intervention and make the final decision to terminate the trial.

The final trial data set will be under the custody of Longhua Hospital/Shanghai University of TCM. The data manager from the clinical evaluation center of Longhua Hospital will have access to the complete, anonymous final data set. Access to the final data set or identifiable data by others will require written requests to be approved by the DSMB of the clinical evaluation center of Longhua Hospital/Shanghai University of TCM and all study investigators.

### Sample size calculation

The sample size was determined using the results of our previous clinical trial and pilot trial [45–47]. The primary efficacy parameter is the change in FMA scores from baseline to the end of treatment after 8 weeks. According to our preliminary test and previous study, the primary efficacy parameter (FMA score) of the control group (rehabilitation treatment) would be increased by 9.86, and that of the treatment group (scalp acupuncture combination rehabilitation treatment) would be increased by 19.12. The FMA average standard deviation would be approximately 7.64. A two-sided 5% significance level and 90% power were considered, and the above relevant data (9.86, 19.12, 7.64, α = 0.05, 1 – β = 0.9) were input into NCSS-PASS V11.0.7 software (https://www.ncss.com/software/pass/) [48]. On the basis of the software calculation, approximately 45 participants are required in each group in order to have a sufficient sample size. With an estimated dropout rate of 20%, each group is required to have 54 initial participants.

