### Study design

This is an outcome assessor- and data analyst-blinded, randomized controlled study. The study is planned to be conducted from 1 January 2015 to 31 December 2016 in Longhua Hospital affiliated with the Shanghai University of Traditional Chinese Medicine. Stroke patients with motor dysfunction meeting the inclusion criteria will be allocated by a 1:1 ratio into either an acupuncture treatment group or a control group. Stroke patients in the control group will receive conventional rehabilitation treatment, whereas a combination of Jao’s scalp acupuncture and conventional rehabilitation treatment will be applied to the acupuncture group. The Fugl-Meyer Assessment (FMA) scale will be assessed as the primary outcome measure. The Modified Barthel Index (MBI), the Stroke-Specific Quality of Life (SS-QOL), and the Stroke Syndrome of Traditional Chinese Medicine (SSTCM) scales will be selected as secondary outcome measurements. All assessments will be conducted at baseline, week 4 (treatment 20), week 8 (treatment 40), week 12 (follow-up), and week 16 (follow-up). Figure 1 summarizes the flow of the entire trial. Figure 2 shows the study timeline, according to the Standard Protocol Items: Recommendations for Interventional Trials (SPIRIT) diagram. Additional file 1 presents the SPIRIT checklist.

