### Primary outcome measurement

#### Fugl-Meyer Assessment (FMA)

The FMA scale for motor function was developed as the first quantitative evaluative instrument for measuring sensorimotor stroke recovery, which includes an assessment of the upper extremities (UE, 33 items) and lower extremities (LE, 17 items) [31]. The FMA scale includes flexor synergy, extensor synergy, movement combining synergies, movement out of synergy, wrist, hand, and coordination/speed. The motor FM assessments are scored on a 3-point ordinal scale (0–2). Each item can be divided into three levels, the lowest level being 0 point, the highest being 2 points, and level between the two indicated with 1 point. The FM motor assessment is used to measure voluntary limb movement. It includes the UE subscale (33 items; score range 0–66) and the LE subscale (17 items; score range 0–34) for a total motor FM score of 100 [32].

The assessment is performed in a quiet area when the patient is maximally alert. The motor domain has well-established reliability and validity as an indicator of motor impairment severity across different stroke recovery time points [33, 34]. The clinical value of the FM assessment is that it provides a hierarchical scale of motor impairment severity; low FM scores indicate greater impairment. A higher FM score for the UE or LE is a clinical indicator of less motor impairment [35, 36]. The minimal clinically important difference (MCID) values [37–39] of the Chinese version of the FMA in motor domain in patients with stroke are 4.58 for UE, 3.31 for LE, and 6.0 for UE plus LE [40]. We set up a standardized procedure for the FM motor assessments, an adequate training program, and a competency assessment for study raters to ensure rater competence across the duration of the trial. The FMA will be assessed at baseline, during the interventions period (at 4 weeks and 8 weeks), and during the follow-up period (at 12 weeks and 16 weeks).

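### The stated inputs give 16 evaluable patients per group, not 45, so the sample size cannot be traced to its own justification

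*Protocol article*

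**What the plan says.** The Sample size calculation section of the protocol article sets out a complete derivation.

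- **Endpoint:** "The primary efficacy parameter is the change in FMA scores from baseline to the end of treatment after 8 weeks".
- **Control group:** the score "of the control group (rehabilitation treatment) would be increased by 9.86".
- **Acupuncture group:** the corresponding figure is "scalp acupuncture combination rehabilitation treatment) would be increased by 19.12".
- **Variability:** "The FMA average standard deviation would be approximately 7.64".
- **Error rates:** "A two-sided 5% significance level and 90% power were considered".

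The section then repeats these five values as the ones entered into PASS and gives the result: "approximately 45 participants are required in each group in order to have a sufficient sample size". An allowance for 20% dropout raises this to 54 per group, 108 in total.

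Two other sections bear on the check. Study design states that patients "will be allocated by a 1:1 ratio into either an acupuncture treatment group or a control group". Statistical analysis names the independent-sample Student t test for normally distributed continuous variables. The FMA section also gives minimal clinically important differences for the scale, ending with "3.31 for LE, and 6.0 for UE plus LE".

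**The concern.** A difference of 9.26 points against an SD of 7.64 is a very large standardised effect, and 45 per group is far more than such an effect needs at 90% power. The article presents 45 as the direct output of the listed values, so a reader should be able to reproduce it.

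If it cannot be reproduced, then taking the listed inputs as complete, the assumed effect, the SD, the power and the group size cannot all be right, and the text does not show which is wrong. If 7.64 is sound, the trial is much larger than its stated assumption requires. If the SD actually used was larger, the trial is much weaker against a difference of clinically important size than a reader would infer, and a null result would say less. The wording adds to the doubt: the endpoint is a change score, but the SD is described only as an average FMA standard deviation and not as the SD of the 8-week change.

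**Working it through.** **Inputs** (Sample size calculation unless noted): mean gains 9.86 and 19.12; SD 7.64; two-sided α = 0.05; power 0.90; 1:1 allocation (Study design); two-sample t test (Statistical analysis).

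**Step 1: effect size.** Difference = 19.12 − 9.86 = 9.26. Standardised effect d = 9.26 / 7.64 = 1.212.

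**Step 2: attempt to reproduce 45.**
- Normal approximation: n = 2(1.960 + 1.2816)² / 1.212² = 14.3, so 15 per group.
- Two-sample t test (noncentral t): n = 15.3, so 16 per group. Power is 0.893 at 15 and 0.913 at 16.

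The stated 45 is not reproduced. It is 45 / 16 = 2.8 times the answer. Allowing for 20% dropout, 16 / 0.8 = 20 per group, or 40 in total, against the stated 108.

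**Step 3: power at the stated size.** With d = 1.212, power is 0.9999 at 45 per group and 0.9998 at 43.

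**Step 4: does another reading of the inputs give 45?** Except in the last two rows, the difference stays at 9.26. Per-group results, by normal approximation or t test:

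| Variant | n per group |
|---|---|
| One-sided 5% | 12–13 |
| 95% power | 18–19 |
| 99% power | 26–27 |
| α = 0.01 | about 22 |
| Bonferroni for 4 or 5 tests | 20–22 |
| Rank test in place of t test | 17–18 |
| 7.64 as a single-visit SD, zero correlation (SD of change 10.8) | 29–30 |
| Difference of 6.0 in place of 9.26 | 35–36 |
| Unstated superiority margin of 4 points (effective difference 5.26) | 45–46 |

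Only the last row reaches 45, and the article mentions no margin.

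**Step 5: what would make 45 the 90% answer?** At n = 45 per group the t test has 90% power for d = 0.691. Holding the SD at 7.64, the difference would be 0.691 × 7.64 = 5.28. Holding the difference at 9.26, the SD would be 9.26 / 0.691 = 13.4. Neither figure appears in the article.

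**Step 6: consequence for a difference of 6.0 points.** The stated 54 less 20% leaves 54 × 0.8 = 43.2, about 43 evaluable per group. The 54 column applies if every randomised patient contributes.

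| SD of change | Power at 43 | Power at 45 | Power at 54 |
|---|---|---|---|
| 7.64 (stated) | 95% | 96% | 98% |
| 13.4 (back-solved) | 54% | 56% | 64% |

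**The case against.** The strongest reply concerns severity, since the arithmetic itself is not in dispute. On the stated inputs the error is conservative: power for 9.26 points exceeds 99.9% at 43, 45 or 54 per group. The SD of 13.4 appears nowhere in the article and is only back-solved from 45. Even with that SD, power for 9.26 would be 89% at 43 and 90% at 45, and the loss appears only when the target becomes 6.0, which the article does not use for sizing. The analysis is to include all randomised patients, so the effective number may be nearer 54 than 43. An unreported 4-point margin would also explain 45 with neither the SD nor the effect being wrong. Finally, the Trial status section says the study is completed, so enrolment cannot change.

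Much of this stands as a limit on the claim. The point does not show that the trial is too small, and the 13.4 case is conditional. A margin is a possible explanation, but it would then be a material input missing from a list presented as what was entered. None of the reply makes the paragraph correct: the listed values do not return 45, and no other section supplies what is missing.

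**Conclusion.** The point holds: the paragraph is wrong as written and must be corrected. The stated inputs require 16 per group by the t test (15 by the normal approximation), against the stated 45. Conversely, 45 per group gives about 99.99% power on those inputs, against the stated 90%. This rests only on the article's own figures and on a standard two-sample comparison of means with equal allocation.

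Which element is at fault cannot be settled from the article. An SD near 13.4, a difference near 5.3 or an unreported margin of about 4 points would each account for 45. The practical range is wide: at 43 evaluable per group, power for 6.0 points is 95% under the stated SD and about 54% under the back-solved one. The second figure is hypothetical and assumes that the SD is the faulty input.

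**What to change.** Retrieve the PASS run and correct the paragraph, keeping 54 per group. There are two ways to do this.

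1. Report the procedure and every input that actually gave 45: the true SD of the 8-week change, the smaller difference, or any margin.
2. If no such run can be found, withdraw the statement that 9.26, 7.64 and 90% power lead to 45, and state what the fixed size provides. For example: 54 randomised per group, about 43 evaluable, gives 95% power to detect 6.0 FMA points with an SD of change of 7.64 at a two-sided 5% level.

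The example sentence should be used only once the sponsor confirms that 7.64 is the SD of the 8-week change. It should be labelled as a description of the power of a size already fixed, not as the original rationale. Under either route the text should say what the SD refers to.

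The cost is one paragraph and one software rerun, with no change in enrolment.

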### Participant recruitment

Participants will be recruited from two hospitals (Longhua Hospital affiliated with the Shanghai University of Traditional Chinese Medicine and the Shanghai Changning District Tianshan Traditional Chinese Medicine Hospital, which is a Longhua Hospital branch) in Shanghai, China. Our study will be propagated via the Internet, local health-related newspapers, and posters in communities and hospitals. Prospective participants will be asked to talk face to face with study coordinators to discuss the study and provide information regarding eligibility criteria. If patients are eligible and interested in participating, they will be invited for a series of rehabilitation assessments after diagnosis by neurologists. One hundred and eight patients will be included in the study. When their informed consent has been obtained, patients will be randomized into two groups with different treatments.

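### The 20% dropout allowance does not fit its own target: 54 per group leaves about 43 completers, not 45 (57 would be needed), with little effect on power

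*Protocol article*

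**What the plan says.** All the figures are in the protocol article, under Sample size calculation. The endpoint is defined there: "The primary efficacy parameter is the change in FMA scores from baseline to the end of treatment after 8 weeks". The control mean "would be increased by 9.86" and the treatment mean "would be increased by 19.12". On spread: "The FMA average standard deviation would be approximately 7.64". On error rates: "A two-sided 5% significance level and 90% power were considered". From these inputs the section reports a software result of about 45 per group and then adds the allowance for losses: "With an estimated dropout rate of 20%, each group is required to have 54 initial participants". It gives no formula for that last step.

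The result is carried forward. Interventions gives 54 in each arm and 108 overall, and Participant recruitment says "One hundred and eight patients will be included in the study". Allocation is 1:1 (Study design). Statistical analysis says that everyone randomised is analysed by intention to treat, with last observation carried forward, and also names a mixed model for missing values.

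**The concern.** A dropout rate is the share of enrolled participants who are lost. The enrolled number must therefore be the required number divided by one minus that rate. Multiplying the required number by one plus the rate gives too few. The three figures 45, 20% and 54 stand in adjoining sentences and cannot all be true: either the loss allowed for is below 20%, or the number left is below 45.

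At stake is whether the stated enrolment delivers the target it was set to protect. A reader who later compares actual attrition with the plan would also take 20% as the loss the design can absorb, when that figure is 16.7%.

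**Working it through.** **Inputs (protocol article, Sample size calculation):** required number 45 per group; dropout 20%; enrolled 54 per group; mean changes 9.86 and 19.12; SD 7.64; two-sided alpha 0.05; power 90%. The 1:1 ratio is from Study design.

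**1. Reproducing the plan's figure.** 45 × (1 + 0.20) = 54.0, an exact match.

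**2. The number needed to keep 45 after 20% loss.** 45 / (1 − 0.20) = 56.25, rounded up to 57 per group, or 2 × 57 = 114 in total. The plan has 54 and 108, which is 3 fewer per group and 6 fewer overall.

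**3. What 54 delivers.**
- At 20% loss: 54 × 0.80 = 43.2, about 43 completers per group, or 86 against the intended 90.
- Largest loss that still leaves 45: 1 − 45/54 = 16.7%.

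**4. Power on the stated inputs.** The difference is 19.12 − 9.86 = 9.26, and the standardised effect is 9.26/7.64 = 1.21. Two-sided t test:

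| Per group | Power |
|---|---|
| 43 | 99.98% |
| 45 | 99.99% |

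**5. The base figure.** With the same inputs, 90% power needs 15.3 per group by the t test, so 16 (15 by the normal approximation). The stated 45 is not reproduced. It would be the 90% answer if the SD were about 13.4 with the difference of 9.26, or if the difference were about 5.28 with the SD of 7.64. Neither value is in the document; both are obtained by solving backwards from 45.

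**6. Power if 45 is taken as the true 90% requirement.** Under either assumption in step 5, 43 per group gives 88.6%, a loss of about 1.4 percentage points.

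**The case against.** The strongest reply is that nothing follows in practice. On the protocol's own inputs about 16 per group would suffice, so 43 and 45 both exceed the need by a wide margin. The 45 is stated as approximate and the dropout rate as an estimate, and a gap of about 2 completers (1.8/45 = 4%) is small beside the uncertainty in either. This stands as a limit on the size of the point. It does not make the three figures agree.

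A reader might infer that the trial is underpowered. The document does not support that: power is above 99.9% on the stated inputs, and the fall to 88.6% needs an SD or a difference that the protocol does not give.

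A reader might also infer that only 43 per group would be analysed. That goes too far. Statistical analysis includes everyone randomised, and Informed consent keeps the data of participants who withdraw. All 54 per group therefore enter the analysis, and the 43 are completers. Carried-forward or modelled values do not carry the information of an observed week-8 score, however, and the allowance itself is there to leave 45 after losses. The shortfall against that target remains.

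One could say that 54 is right for a base of 43, since 43/0.8 = 53.75. But the protocol states 45. That 54 was obtained by multiplying by 1.2 is an inference from the exact match, as no formula is shown. The inconsistency does not depend on it.

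Finally, the point could be folded into the larger problem that 45 does not follow from its inputs. The two are linked, but correcting the base alone would leave an unsound inflation step: multiplying by 1.2 falls short of a 20% loss whatever the base.

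**Conclusion.** The dropout step is arithmetically wrong as written. Keeping 45 per group after 20% loss needs 57 per group (114 in total). The stated 54 (108 in total) keeps 45 only at up to 16.7% loss and leaves about 43 completers per group at 20%. This rests on the usual meaning of a dropout rate, as a share of those enrolled, and on taking the stated 45 as the target.

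The consequence is small: about 2 completers per group, and no material loss of power on the stated difference and SD. Power falls below the planned 90% only on the assumption that 45 is the true requirement, and then to about 88.6%. It is a correction to the stated justification and does not cast doubt on the trial's ability to detect the effect it assumes. The total of 108 is simply 2 × 54, so its repetition elsewhere adds no further error. The larger question in the same section is why the stated inputs, which give about 16 per group, are reported as giving 45.

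**What to change.** Keep 108. Trial status reports the study as completed, so enrolment cannot usefully change. Replace the sentence on dropout with wording such as: 54 per group retains 45 completers if dropout is at most 16.7%, or about 43 if it is 20%; all 54 per group enter the intention-to-treat analysis.

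Then reconcile the base figure of 45 with the difference, SD, alpha and power given for it, either by correcting the inputs or by explaining the larger number. Once that is settled, state the power for 43 completers per group. Power cannot be fixed before then, because it is 99.98% on the inputs as printed and about 88.6% if 45 is the true 90% requirement.

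The dropout correction costs one sentence and no patients, and the stated retention becomes slightly less favourable. The power statement needs the base calculation to be rechecked first.

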### Participant recruitment

Participants will be recruited from two hospitals (Longhua Hospital affiliated with the Shanghai University of Traditional Chinese Medicine and the Shanghai Changning District Tianshan Traditional Chinese Medicine Hospital, which is a Longhua Hospital branch) in Shanghai, China. Our study will be propagated via the Internet, local health-related newspapers, and posters in communities and hospitals. Prospective participants will be asked to talk face to face with study coordinators to discuss the study and provide information regarding eligibility criteria. If patients are eligible and interested in participating, they will be invited for a series of rehabilitation assessments after diagnosis by neurologists. One hundred and eight patients will be included in the study. When their informed consent has been obtained, patients will be randomized into two groups with different treatments.

### Randomization and allocation concealment

Prior to treatment, each patient will be randomly assigned one serial number using a software program. Assignments will be sealed in opaque envelopes and will be opened by the researchers following informed consent procedures and baseline testing. All rehabilitation therapists, assessors, and analysts will be blinded to group assignments.

### Statistical analysis

All data will be analyzed in the clinical research center of Longhua Hospital, affiliated with the Shanghai University of TCM by statisticians using the Statistical Product and Service Solutions (SPSS ) statistical package program (version 17.0, SPSS Inc., Chicago, IL, USA). Baseline assessments will be conducted before randomization, including gender and age of patients, disease course, hemiplegia (left or right), stroke risk factors, diseased location and size, primary outcome (FMA), and secondary outcomes (MBI, SS-QOL, and SSTCM). All patients randomized to each group are included in the analysis, and the data analysis will be conducted using two-sided significance tests at a 5% significance level. All analyses will be based on the intention-to-treat principle using the last observation carried forward rule. Missing values will be handled by the mixed model for repeated measurements. Continuous variables with normal distribution will be expressed as means with standard deviations (SDs) and compared by an independent sample Student *t* test. For abnormally distributed variables, the data will be expressed as medians with ranges, and non-parametric tests will be used. Categorical variables will be expressed as number (%) and analyzed by *χ*
^2^ test or Fisher’s exact test. Descriptive statistics will be used to detail baseline participant demographics and general status characteristics of patients, such as gender, age, disease course, hemiplegia (left or right), stroke risk factors, and diseased location and size. Repeated measures analysis of variance (ANOVA) will be used to analyze value changes of FMA, MBI, SS-QOL, and SSTCM scores across five testing time points (weeks 0, 4, 8, 12, and 16). Safety analyses will be compared with the incidence of AEs in the two groups using the *χ*
^2^ test.

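### The plan sets two incompatible missing-data rules, LOCF for all analyses and a mixed model for missing values, without saying which is primary; LOCF is the poorer of the two here

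*Protocol article*

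**What the plan says.** The Statistical analysis section of the protocol article defines the analysis set: "All patients randomized to each group are included in the analysis". It then gives two rules for missing data in consecutive sentences: "All analyses will be based on the intention-to-treat principle using the last observation carried forward rule" and "Missing values will be handled by the mixed model for repeated measurements". Neither is called primary or sensitivity, and neither is tied to a particular outcome or visit.

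The tests named afterwards are different again. Normally distributed continuous variables are to be "compared by an independent sample Student *t* test". For the course over the five assessment times, "Repeated measures analysis of variance (ANOVA) will be used to analyze value changes of FMA, MBI, SS-QOL, and SSTCM scores". No mixed model appears among the named comparisons.

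The Sample size calculation section fixes the endpoint: "The primary efficacy parameter is the change in FMA scores from baseline to the end of treatment after 8 weeks". It expects gains of 9.86 in control and 19.12 in acupuncture with an SD of about 7.64, and reaches 54 per arm "With an estimated dropout rate of 20" per cent.

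**The concern.** The two rules do different things to the same patients. LOCF replaces every missing later visit with the last score seen and then treats the data as complete. A mixed model for repeated measurements uses only the observed scores and fills nothing in. Because the LOCF sentence covers all analyses, the mixed-model sentence has nothing left to act on. An analysis plan written later could not follow both.

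The choice matters because scores are expected to rise in both arms. A patient last seen at baseline is credited with no gain, and one last seen at week 4 with only part of it. What LOCF does to the treatment difference then depends on how many patients leave each arm and when. If the rule stays open, it can be chosen after both answers are known.

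**Working it through.** **Inputs from the document.** Gain to week 8: control 9.86, acupuncture 19.12. SD 7.64. Overall dropout 20%. 54 per arm. Planned difference: 19.12 − 9.86 = 9.26.

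**Inputs assumed, because the document gives none.** Dropout by arm, and f, the share of the week-8 gain already reached at a dropout's last visit (0 if last seen at baseline; 0.5 at week 4 if the gain is linear; 0.75 as a favourable case). Dropout is taken as random within arm.

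**Expected LOCF change in an arm** with gain g and dropout d: g × (1 − d + d·f).

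*Equal dropout, 20% in each arm:*
- f = 0: 19.12 × 0.80 − 9.86 × 0.80 = 15.30 − 7.89 = 7.41
- f = 0.5: 19.12 × 0.90 − 9.86 × 0.90 = 17.21 − 8.87 = 8.33 (from unrounded terms)
- f = 0.75: 19.12 × 0.95 − 9.86 × 0.95 = 18.16 − 9.37 = 8.80 (from unrounded terms)

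The shortfall against 9.26 is 1.85 to 0.46 points.

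*Assumed unequal dropout:*

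| Acupuncture / control | f = 0 | f = 0.5 | f = 0.75 |
|---|---|---|---|
| 30% / 10% | 13.38 − 8.87 = 4.51 | 6.88 | 8.07 |
| 10% / 30% | 17.21 − 6.90 = 10.31 | 9.78 | 9.52 |

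**No true effect (both arms gain 9.86).** The spurious difference is 9.86 × (difference in dropout) × (1 − f). For 10% against 30% it is 9.86 × 0.20 = 1.97 at f = 0 and 0.99 at f = 0.5. Simulated rejection rates for a two-sided 5% t test, 54 per arm, SD 7.64:
- 20% / 20%: about 5%
- 10% / 30%, all last seen at baseline: about 26%
- 10% / 30%, half leaving before week 4 and half after: about 17%
- 10% / 30%, all carrying half the gain: about 10% to 11%
- 15% / 25%, all last seen at baseline: about 10%

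**Comparison with the other rule.** A likelihood estimate for monotone missing data, which is the principle of the mixed model, was simulated with the planned gains. It assumed a linear gain, half of dropouts leaving before week 4, a week-4 SD of 5.5 and a correlation of 0.7 between the week-4 and week-8 changes. It gave 9.23 to 9.27 under 20/20, 30/10 and 10/30 (acupuncture/control). LOCF gave 7.83, 5.69 and 10.05 in the same runs. The two printed rules therefore give different primary results.

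**The case against.** The size of the harm depends on inputs that are not in the document. It gives one overall dropout rate, no split by arm and no week-4 FMA value. The 26% needs a threefold imbalance with every dropout carried at zero gain. In the case closest to the plan, equal 20% dropout, type I error stays at 5%. LOCF then only dilutes the effect, and power on the planned gains is still about 98% even with all dropouts carried at baseline. Reasons for unequal dropout can be imagined in either direction, so no net direction of bias is shown. All of this stands and limits the claim. It does not remove the contradiction, or the dilution under equal dropout.

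Two stronger readings are tempting and are not supported.

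- *That LOCF understates the standard error.* This is not generally so. With planned gains, 20% / 20% dropout and baseline carried forward, the variance in an arm is (1 − d)·SD² + d(1 − d)·g², which is 105.2 for acupuncture and 62.3 for control. The standard error is √((105.2 + 62.3)/54) = 1.76. For completers only it is 7.64 × √(2/43.2) = 1.64. LOCF is the larger here; it is smaller in the no-effect case with 10% / 30% (1.51 against 1.66).
- *That LOCF hides deterioration after a recurrent stroke.* The data monitoring section lists "having a recurrent stroke, having serious complications of stroke or experiencing serious acupuncture-related AEs" as grounds for unblinding and stopping the allocated intervention. It does not say that assessment stops. If assessment did stop, a mixed model assuming data missing at random would project continued recovery for that patient and hide the deterioration too. The example does not separate the two rules.

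It may also be said that model details belong in a separate analysis plan. That is fair for the covariance structure, but not for two conflicting rules that the article itself prints.

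**Conclusion.** The concern holds as a contradiction in the printed text and as a poor choice of rule. LOCF and the mixed model are both prescribed, unranked, for the same missing values. On the plan's own gains and 20% dropout, LOCF lowers the expected week-8 difference from 9.26 to about 7.4 to 8.8 when dropout is equal. The range of 4.5 to 10.3, and the type I error of about 10% to 26%, apply only under the assumed 10% / 30% imbalance and depend on when patients leave. They show how sensitive LOCF is and do not predict this trial. The direction of bias is not fixed. The result does not depend on any gain after week 8. The mixed model's advantage rests on data being missing at random given the observed scores.

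**What to change.** In the Statistical analysis section:

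1. Keep the intention-to-treat statement for all randomised patients, and remove only the clause that applies LOCF. Deleting the whole sentence would also delete the only statement of the intention-to-treat principle.
2. Name one primary analysis: a mixed model for repeated measurements on observed FMA, with baseline FMA as a covariate and the week-8 treatment contrast as the primary test.
3. Align the t-test and repeated-measures ANOVA sentences with that choice, so that they no longer describe a competing analysis of FMA.
4. Keep LOCF at most as a labelled sensitivity analysis, and add one that probes the missing-at-random assumption.

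The cost is a few sentences of redrafting and reliance on the missing-at-random assumption. The Trial status section says that the study is complete. If the analysis has already been run, the report should state which rule produced the primary result, show the other beside it, and give dropout by arm and visit so that readers can judge the difference.
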